### Sample size

Our primary outcome variable is the number of incidents of victimization (count data); therefore, a Poisson distribution is assumed. A priori sample size calculation was performed under this assumption, using the asypow package for R 3.0. Since we are the first to examine effects of an intervention aimed at reducing revictimization in depressed patients, it is difficult to determine an exact estimate of the effect size for the main outcome measure. We expect that patients in the experimental condition will have experienced 30% less incidents at the endpoint in comparison with patients in the control condition, which we consider a realistic and clinically meaningful effect.

A previous study showed that 34% of depressed patients had been victim of at least one violent crime during one year [17]. On average, these patients had been victim of 3.30 (SD = 4.32) violent crimes in a one-year period – after two outliers (2%) who reported an extremely high number of incidents were deleted. Based on these results, we calculated that the expected average number of incidents over a period of 12 months after baseline, in a subsample of recently victimized patients, will be 3.0. Since the observed variance in the previous study indicated an overdispersed Poisson distribution, we performed numerical simulation in R for our sample size calculation, with adjustment for the expected overdispersion. Based on this simulation, we will need a minimum of 95 patients in each condition to demonstrate a difference between conditions of 30% in total incidents with α = .05, two-sided, and 1-β = .80. To account for missing information due to patient dropout, we aim to include 200 patients in total.

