#### Randomization and procedure

Randomization will be carried out after completion of the first part of the baseline assessment. Randomization of participants in every participating site will be performed by a research associate of the data management department of GGZ inGeest, who is not familiar with the subject, nor involved in providing any kind of mental health care. Randomization will take place at an individual level, stratified by mental health care site, using a computer-generated block randomization schedule. To ensure that an equal number of patients will be allocated to TAU and TAU + iERT, the allocation ratio will be 1:1. To prevent selection bias, researchers and outcome assessors will be blind to block size and order, and will not have access to the randomization schedule. Due to the nature of treatments, blinding of participants and therapists to treatment condition is not feasible. Blinding research assistants to treatment allocation is not applicable to most outcome measures, since these will be administered online. Research assistants responsible for administering the MINI interview by telephone at 12 months after baseline will be blinded to treatment allocation. To promote data quality, all research assistants will be trained in administering the MINI interview. Audio recordings will be made of every MINI interview, which will be used in supervision sessions. Since all other measures concern web-based questionnaires that are filled out by the participants themselves, double data entry procedures are not applicable.

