During the treatment phase, assessments will be administered at 8 weeks, 14 weeks, and 6 months after start of TAU in both the experimental and the control group. Follow-up assessments will be administered at 12, 24, and 36 months after the first baseline assessment. Except for the MINI, which will be assessed in a telephone interview at 12 months after baseline, all assessments will be conducted online. Patients receive an e-mail with a link to the self-report questionnaires, and those who have not completed an assessment within 4 days will receive a reminder via e-mail. Patients who have not completed the assessments after one week will be approached via telephone by a research assistant. If necessary, online assessments can also be completed over the telephone by an assistant who is blinded to treatment condition. Participants will be compensated with a voucher of 15 euros per assessment for both the first and second part of T0, T1, T2, T3, T5 and T6, and a voucher of 30 euros for T4.

Additional questionnaires will be sent out in the TAU + iERT condition: a visual analogue mood scale (VAMS) is to be completed online after every iERT-session in the online treatment platform, and the System Usability Scale (SUS) and Technical Alliance Inventory (TAI) are to be filled out after completion of iERT. The SUS will also be sent out once to each iERT-therapist. Table 1 provides an overview of all instruments per assessment.

**Table 1 Tab1:** Overview of instruments per assessment

Instrument	T0_1_	T0_2_	T1	T2	T3	T4	T5	T6^a^
Mini International Neuropsychiatric Interview	x					x		
Safety Monitor	x					x	x	x
Inventory of Depressive Symptomatology	x		x	x	x	x	x	x
Difficulties in Emotion Regulation Scale	x		x	x	x	x	x	x
Visual Analogue Mood Scale	x		x^b^	x	x	x	x	x
Positive and Negative Affect Schedule	x		x	x	x	x		
Demographic questionnaire	x							
Posttraumatic Diagnostic Scale		x			x			
Childhood Trauma Questionnaire	x							
List of Threatening Experiences		x						
Brief Symptom Inventory		x			x			
Utrechts Coping List		x				x		
Ruminative Response Scale		x	x	x	x	x		
Pearlin Mastery Scale		x	x	x	x	x		
Dysfunctional Attitude Scale		x	x	x	x	x		
Self-Esteem Rating Scale	x							
Inventory of Interpersonal Problems		x				x		
NEO Five Factor Inventory			x					
EuroQol 5D-5 L	x				x	x		
Trimbos questionnaire on Costs associated with Psychiatric Illness	x				x	x		
Working Alliance Inventory				x				
Client Satisfaction Questionnaire				x				

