## Discussion

This paper describes the study protocol of a randomized controlled trial aimed at assessing the effectiveness of the addition of iERT to TAU in reducing violent revictimization, depressive symptoms, and emotion regulation difficulties in previously victimized, depressed patients. Despite the high prevalence rates and societal burden of victimization in psychiatric patients, there remains a paucity of knowledge of risk factors and predictors regarding violent victimization in depressed patients. Accordingly, evidence-based interventions aimed at reducing victimization and revictimization are still scarce. To the best of our knowledge, this study is the first to examine the effectiveness of an intervention aimed at reducing revictimization in depressed patients. We will investigate the hypotheses that the addition of iERT to TAU is effective and cost-effective in decreasing incidents of revictimization in depressed patients compared to TAU alone. Furthermore, this study will examine whether the addition of iERT to TAU leads to a significant improvement on secondary outcome measures. If iERT is effective in reducing incidents of revictimization, it can be implemented in mental health care.

Major strengths of the current study are the long follow-up period of 36 months and the large amount of validated, clinically relevant outcome measures that are administered at multiple assessments during the treatment phase, which enables us to gain insight into the underlying mechanisms of revictimization. The most important concern of this study will be treatment adherence, since internet-based treatments are associated with high dropout levels [102, 103]. Weekly therapist guidance and the relatively small amount of iERT-sessions is expected to enhance treatment adherence, but it will remain an important challenge of this trial. To prevent study dropout, participants will receive monetary compensation for all assessments.

In conclusion, the prospective and longitudinal design of this study provides a unique opportunity to thoroughly examine revictimization rates and a variety of relevant secondary outcomes, mediators, and moderators over a period of three years.

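### The stated 80% power holds only if at least 95% of patients give a 12-month count; a short telephone fallback would protect that count

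*Protocol article*

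**What the plan says.** All references are to the protocol article.

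- **Sample size:** "we will need a minimum of 95 patients in each condition to demonstrate a difference between conditions of 30% in total incidents". The calculation is for 80% power at a two-sided 5% level. The enrolment target follows: "To account for missing information due to patient dropout, we aim to include 200 patients in total". No dropout percentage is given.
- **Primary outcome measure:** the endpoint is the total number of violent incidents reported on the Safety Monitor at T4, 12 months after baseline. The frequency questions cover the preceding 12 months.
- **Table 1:** the Safety Monitor appears at T0, T4, T5 and T6, and at none of T1 to T3. Thirteen instruments are marked at T4. Twelve are online questionnaires and one, the MINI, is a telephone interview.
- **Randomization and procedure:** an e-mail reminder goes out after 4 days, and then "Patients who have not completed the assessments after one week will be approached via telephone by a research assistant". Online assessments may be completed by telephone with a blinded assistant. The voucher is 30 euros at T4 and 15 euros at the other assessments. No reduced set of questions is described.
- **Data analysis, Effectiveness:** the primary analysis is by intention to treat, with multiple imputation for missing data.
- **Discussion:** "The most important concern of this study will be treatment adherence, since internet-based treatments are associated with high dropout levels". Study dropout is mentioned separately, with payments as the measure to prevent it.

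**The concern.** The enrolment target exceeds the required number by five patients per arm. That margin has to cover every patient without a usable count a year after baseline, in depressed outpatients facing a long T4 assessment. The article gives no rate by which to judge whether the margin is enough.

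The primary outcome is also measured only once in the primary year. If T4 is missed, no earlier follow-up count stands behind it. A patient who returns at T5 reports on the 12 months before T5, not on the primary year. Multiple imputation can draw on other variables and on any later count, but it recovers only part of the information. Each missing T4 count therefore costs the primary comparison close to a full patient, and once more than ten are missing the sample is below the number the plan calls its minimum.

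**Working it through.** **Inputs, all from the protocol article.** Required number: "we will need a minimum of 95 patients in each condition". Enrolled: 200, and "the allocation ratio will be 1:1", so 100 per arm. Effect: "patients in the experimental condition will have experienced 30% less incidents at the endpoint", a rate ratio of 0.70. Control mean 3.0, so 2.1 under iERT. Two-sided alpha 0.05, power 0.80. Prior study: mean 3.30, SD 4.32. Dropout rate: not stated, so a range is assumed.

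**Step 1: the allowance.** 2 × 95 = 190, and 1 − 190/200 = 0.05. In the other direction, 95/(1 − 0.05) = 100 per arm. The target of 200 is exactly a 5% inflation.

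**Step 2: power when T4 counts are missing.** Take 95 per arm = 80% as given, and let a missing count contribute nothing. With n = 100 × (1 − d) per arm,

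power = Φ(√(n/95) × (1.960 + 0.842) − 1.960).

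Example at d = 20%: √(80/95) = 0.918; 0.918 × 2.802 = 2.571; 2.571 − 1.960 = 0.611; Φ(0.611) = 0.729.

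| Assumed share without T4 count | n per arm | Power | Total needed for 80%, 2 × 95/(1 − d), each arm rounded up |
|---|---|---|---|
| 0% | 100 | 82.0% | 190 |
| 5% | 95 | 80.0% | 200 |
| 10% | 90 | 77.8% | 212 |
| 15% | 85 | 75.5% | 224 |
| 20% | 80 | 72.9% | 238 |
| 25% | 75 | 70.2% | 254 |

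The shortfall reaches 5 points at about 16% missing.

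**Step 3: does the base of 95 reproduce?** On the log rate-ratio scale, n per arm = (1.960 + 0.842)² × V / (ln 0.7)², with (ln 0.7)² = 0.1272.

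- Pure Poisson: V = 1/3.0 + 1/2.1 = 0.810, so n = 50.
- Quasi-Poisson: variance/mean = 4.32²/3.30 = 5.66, so V = 0.810 × 5.66 and n = 283.
- Negative binomial: dispersion = (4.32² − 3.30)/3.30² = 1.41, so V = 0.810 + 2 × 1.41 and n = 225.

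None of these gives 95. A figure of 95 needs a variance/mean ratio of about 1.90 (95/49.9), far below 5.66. With the printed dispersion allowed for, power at 95 per arm is about 37% (quasi-Poisson) to 45% (negative binomial). The article does not state which dispersion its simulation used, and it leaves open whether the SD applies to victims only. This is a separate issue, but it means that the table in step 2 is conditional.

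**The case against.** The case for the plan is substantial. Its numbers are consistent: 95/0.95 is 100, so there is no arithmetic error. A condensed article may leave the reasoning behind a dropout rate to the full protocol. Retention is not neglected either, given the reminders, telephone contact, telephone completion, a doubled voucher at T4 and a telephone MINI interview at the same time point. The power loss is modest at moderate rates, and the figures rest on a base that could not be reproduced. All of this stands.

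A reader might infer that the plan contradicts itself, by expecting heavy dropout while allowing 5%. The Discussion does not support that. The challenge it describes is adherence to iERT, which only one arm receives. A patient who stops iERT but answers at T4 stays in the intention-to-treat analysis with a count. Paying participants to prevent study dropout does not forecast a high rate of it.

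A reader might also infer that the 80% power is lost at ordinary attrition. The article gives no figure for ordinary attrition, and the decline is gradual.

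What remains is narrower. The 5% allowance is unexplained, the single primary count has no earlier follow-up measurement behind it, and the planned telephone contact has no stated minimum for a patient who will not do the whole battery.

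**Conclusion.** The point holds in limited form. The stated 80% power allows exactly 5% of patients, 10 of 200, to lack a T4 count, and the article gives no expected rate. Beyond 5%, power falls to about 78% at 10% missing, 75% at 15% and 73% at 20%. Three assumptions lie behind those figures: the missing rates are illustrative, missing counts add no information, and 95 per arm truly gives 80%. The last does not follow from the printed mean and SD.

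This is not an internal contradiction, and it does not show that the trial will miss its power. It is an opportunity for a cheap improvement: ten recovered T4 counts would be worth as much as the whole dropout allowance.

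**What to change.** 1. **Randomization and procedure.** Add a minimum data set for T4. If a patient declines or does not complete the full battery at the telephone contact already planned, the blinded assistant takes at least the Safety Monitor violent-crime items: for physical assault, sexual assault and threat, whether each occurred in the past 12 months and how often. Record the mode of collection. Use these counts in the primary analysis, with a sensitivity analysis by mode.
2. **Sample size.** Add one sentence stating that 80% power assumes a T4 count from at least 95% of patients. Do not print the lower power figures above until the base of 95 per arm has been verified.
3. **Optional.** At T5, ask patients who missed T4 about the missed year. This asks them to recall events from 12 to 24 months earlier, so it suits a sensitivity analysis only and cannot restore primary power.

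The cost is a few lines of text and a short script for a call already planned, with no extra patients. The downside is mixed mode of collection, since answers on violence may differ between telephone and online. The plan already permits telephone completion, so the mixing is not new, and recording the mode lets it be examined.

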### Procedure

#### Recruitment and consent

Participants will be recruited at the mood and anxiety disorder departments of GGZ inGeest and Arkin: the two largest mental health institutes in Amsterdam, the Netherlands. All patients referred to one of the participating sites will be screened for eligibility by a clinician during regular intakes, and all eligible patients will receive written study information directly after intake. Patients who agree to be approached by a researcher will be contacted by telephone after one week by a research assistant, who will provide further information about participation in the study and will make an appointment for the screening interview. The screening will preferably take place within one to maximum four weeks before the patient starts with TAU, and will be performed either by telephone or face-to-face – depending on the patient’s preference.

At the screening, inclusion and exclusion criteria will be assessed in detail by a research assistant. First, the MINI International Neuropsychiatric Interview (MINI 5.0) [50] will be administered to assess a current diagnosis of depression and other Axis I disorders. In addition, three slightly adapted questions of the Safety Monitor addressing the experience of three types of violent crime (physical assault, sexual assault, or threat) will be asked. A definition and examples of each type of crime will be provided. If the patient reports having experienced at least one violent crime over the past three years, he or she will be asked to briefly describe the crime to ensure that he or she was violently victimized. All patients who meet the criteria will sign an informed consent prior to the first assessment, and will be included in the study. To decrease the burden for participants, the baseline assessment will be divided into two parts that both consist of online administered self-report questionnaires. The first part is to be completed within one week after the screening, and the second part is to be completed preferably within a week after the first part. Figure 1 provides an overview of the trial design.

**Fig. 1 Fig1:**
[figure not shown]
Trial flow chart

#### Randomization and procedure

Randomization will be carried out after completion of the first part of the baseline assessment. Randomization of participants in every participating site will be performed by a research associate of the data management department of GGZ inGeest, who is not familiar with the subject, nor involved in providing any kind of mental health care. Randomization will take place at an individual level, stratified by mental health care site, using a computer-generated block randomization schedule. To ensure that an equal number of patients will be allocated to TAU and TAU + iERT, the allocation ratio will be 1:1. To prevent selection bias, researchers and outcome assessors will be blind to block size and order, and will not have access to the randomization schedule. Due to the nature of treatments, blinding of participants and therapists to treatment condition is not feasible. Blinding research assistants to treatment allocation is not applicable to most outcome measures, since these will be administered online. Research assistants responsible for administering the MINI interview by telephone at 12 months after baseline will be blinded to treatment allocation. To promote data quality, all research assistants will be trained in administering the MINI interview. Audio recordings will be made of every MINI interview, which will be used in supervision sessions. Since all other measures concern web-based questionnaires that are filled out by the participants themselves, double data entry procedures are not applicable.

During the treatment phase, assessments will be administered at 8 weeks, 14 weeks, and 6 months after start of TAU in both the experimental and the control group. Follow-up assessments will be administered at 12, 24, and 36 months after the first baseline assessment. Except for the MINI, which will be assessed in a telephone interview at 12 months after baseline, all assessments will be conducted online. Patients receive an e-mail with a link to the self-report questionnaires, and those who have not completed an assessment within 4 days will receive a reminder via e-mail. Patients who have not completed the assessments after one week will be approached via telephone by a research assistant. If necessary, online assessments can also be completed over the telephone by an assistant who is blinded to treatment condition. Participants will be compensated with a voucher of 15 euros per assessment for both the first and second part of T0, T1, T2, T3, T5 and T6, and a voucher of 30 euros for T4.

Additional questionnaires will be sent out in the TAU + iERT condition: a visual analogue mood scale (VAMS) is to be completed online after every iERT-session in the online treatment platform, and the System Usability Scale (SUS) and Technical Alliance Inventory (TAI) are to be filled out after completion of iERT. The SUS will also be sent out once to each iERT-therapist. Table 1 provides an overview of all instruments per assessment.

**Table 1 Tab1:** Overview of instruments per assessment

Instrument	T0_1_	T0_2_	T1	T2	T3	T4	T5	T6^a^
Mini International Neuropsychiatric Interview	x					x		
Safety Monitor	x					x	x	x
Inventory of Depressive Symptomatology	x		x	x	x	x	x	x
Difficulties in Emotion Regulation Scale	x		x	x	x	x	x	x
Visual Analogue Mood Scale	x		x^b^	x	x	x	x	x
Positive and Negative Affect Schedule	x		x	x	x	x		
Demographic questionnaire	x							
Posttraumatic Diagnostic Scale		x			x			
Childhood Trauma Questionnaire	x							
List of Threatening Experiences		x						
Brief Symptom Inventory		x			x			
Utrechts Coping List		x				x		
Ruminative Response Scale		x	x	x	x	x		
Pearlin Mastery Scale		x	x	x	x	x		
Dysfunctional Attitude Scale		x	x	x	x	x		
Self-Esteem Rating Scale	x							
Inventory of Interpersonal Problems		x				x		
NEO Five Factor Inventory			x					
EuroQol 5D-5 L	x				x	x		
Trimbos questionnaire on Costs associated with Psychiatric Illness	x				x	x		
Working Alliance Inventory				x				
Client Satisfaction Questionnaire				x				
Technical Alliance Inventory				x^c^				
System Usability Scale				x^c^				

^a^*T0*_*1*_*:* baseline part 1, *T0*_*2*_*:* baseline part 2, *T1:* 8 weeks after start of TAU, *T2:* 14 weeks after start of TAU, *T3:* 6 months after start of TAU, *T4:* 12 months after baseline, *T5:* 24 months after baseline, *T6:* 36 months after baseline

^b^Will also be assessed after each iERT-session in the experimental group

^c^Will only be assessed in the experimental group

### Interventions

#### Internet-based emotion regulation training (iERT)

The experimental intervention, iERT, is an abbreviated and slightly adapted online version of the Affect Regulation Training (ART) [44]. ART is a transdiagnostic structured group intervention that aims to enhance emotion regulation skills and consists of techniques from dialectical behavioral therapy, Systems Training for Emotion Predictability and Problem Solving program (STEPPS), emotion-focused therapy, Cognitive Behavioral Therapy (CBT), mindfulness-based interventions, self-compassion trainings, and problem-solving therapies. Although ART uses some techniques that are also included in CBT, ART explicitly and exclusively focuses on enhancing emotion regulation skills as opposed to CBT, which mainly targets cognitive and behavioral antecedents of depression [51]. In ART, the patient acquires seven emotion regulation skills, which the patient learns to use one-by-one by means of psycho-education and exercises. Subsequently, the patient practices each newly acquired skill in combination with previous skills using an audio file that guides him or her through the cycle of acquired skills [51].

To develop an online version of ART for patients with a major depressive disorder in specialized mental health care institutes in the Netherlands, ART was first translated into the Dutch language by an educated medical translator. Subsequently, the material was abbreviated and simplified, since all depression experts whom we consulted considered the original version too complicated and extensive for online use in moderately to severely depressed patients. iERT therefore focuses on a selection of four instead of seven skills: (1) non-judgmental awareness of emotions (*Awareness*); (2) acceptance and tolerance of emotions (*Acceptance*); (3) analysis of emotions (*Analysis*); and (4) active modification of emotions (*Modulation*). This selection was based on a literature review that we conducted, which indicated these emotion regulation skills to be highly relevant for both depressed patients [33, 35] and victimized patients [32, 52]. Lastly, in consultation with the developers of ART, we translated the Dutch, abbreviated protocol into an online version that will be provided on a secured online platform.

iERT consists of 6 sessions of approximately 30 min. After each session, a trained psychologist will provide feedback and guidance using secured e-mail within the online platform. In iERT, general psycho-education about the four skills and the origin, functions, and characteristics of emotions is offered in videos. These videos take 3 to 8 min to watch, and are designed to provide information in a clear, comprehensible, and visually attractive manner. Each session starts with one or two short psycho-education videos, followed by an exercise. Each session ends with an audio file exercise that combines the newly acquired skill with the previous skills. The participant is stimulated to practice with the audio file exercise at least once per week. When participants have mastered the skills by means of in-session theory, examples and exercises, their iERT-therapist stimulates them to start practicing their skills in daily life. The first iERT-session will be introduced in the experimental condition after the fourth session of TAU; from that moment on, the iERT-sessions will run parallel to TAU. A new session will become available weekly, provided that the participant has completed the previous session. The therapists will monitor whether their patients have worked through the previous session in time, and will contact them within two weeks if they have not.

